### Sample size calculation

Power/sample size calculations were made on the basis of an unadjusted Cox proportional hazards regression model. Within the primary analysis of aim 1, assuming a loss to follow-up of 20%, 570,000 subjects (285,000 with AF and 285,000 without) would have 90% power to detect a hazard ratio of 2, at an alpha of 0.05. This conservatively assumes an event rate of 22/100,000 per year in the exposed group (a rate of 45/100,000 is reported previously) [10] and an event rate of 11/100,000 per year in the unexposed group (a rate comparable to that reported previously) [15]. A query of the Medicare 5% sample between 2000 and 2015 reveals 818,940 unique patients with AF and 11,400 unique patients with a new diagnosis of CRAO. Power calculations were performed with the *powerSurvEpi* package (R v4.0.3).

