### Inclusion and exclusion criteria (Aim 1)

The inclusion criterion is continuous fee-for-service Medicare enrollment for at least 12 months prior to AF diagnosis or matched index date (July 1 of inclusion year) for controls and continuous enrollment in fee-for-service (FFS) Medicare after AF diagnosis/index date for at least 12 months or until death if death occurred before 12 months of continuous enrollment.

Patients with prevalent AF will be identified as follows:ICD-9-CM code 427.31 or ICD-10-CM code I48 in 2 outpatient claims or 1 inpatient claim within 365 days, in any diagnosis position of the claim [16–18]. The index date will be the date of the first qualifying inpatient claim or second qualifying outpatient claim. Patients will be required to have 12 months of FFS claims without an AF diagnosis prior to the index AF claims based on inclusion criteria.

Exclusion criteria are:

patients with any claim for CRAO in the 12 months prior to AF diagnosis or index date for controls (July 1 of potential inclusion year).

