### Analytical cohort

An analytic cohort will be generated by applying the below inclusion and exclusion criteria as follows:

All patients meeting the criteria for AF in the study period and meeting other inclusion/exclusion criteria will be identified as cases, and the date of AF diagnosis will serve as case’s index date for calculation of covariates. All remaining beneficiaries will be considered potential controls; inclusion and exclusion criteria will be applied based on an index date of July 1 for each year in the study period; all beneficiaries meeting inclusion/exclusion criteria for each year will be included in the potential control pool. For all potential controls with multiple index dates/years of eligibility, the year they contribute will be selected randomly. A multivariable logistic regression analysis will be conducted using cases and potential controls to create propensity scores for AF status; the final control group will be selected using propensity score matching to the AF cases.

Survival time for patients will be defined as the number of months from the index date when criteria were met. Patients will be censored at death, at the end of fee-for-service enrollment, or at the end of data availability. When 85% of the cohort has died or been lost to follow-up, we will censor remaining patients at that point to avoid instability in estimates due to very small numbers of remaining participants.

Details of the cohort analysis will be reported using RECORD guidelines for analyses of routinely collected data, including use of a patient flow diagram [24].

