#### Regression modeling (aim 1)

a) The study index date will be the date of the first AF claim in the study and July 1 in the first year of inclusion in the analytic cohort for controls for the purposes of our survival analysis.b) We will describe cumulative incidence of CRAO over time with the overlap-weighted cumulative incidence function and presented graphically for patients with and without atrial fibrillation. Next, a weighted, unadjusted cause-specific hazard model will be fit with AF as the univariable predictor and CRAO as the event of interest, with patients censored at death, at end of data availability, or at end of fee-for-service Medicare enrollment.c) Then, a weighted cause-specific hazard model, clustered by state, and adjusting for age, sex, race, cardiovascular comorbidities will be fitted. Directly adjusted cumulative incidence curves for AF and control patients will be created with adjustment for all model covariates [28].d) We will test the proportional hazards assumption for all models.e) Our primary analytical model will be an overlap-weighted model with propensity scores derived from the adjustment covariates previously described as predictors for the presence of atrial fibrillation. We will report our results with sequential adjustment to produce the fully-adjusted, weighted model. We employ this sequential adjustment strategy to provide insight as to sources of measured confounding.f) We will evaluate **positive control endpoints**. Our positive control endpoints will be any ischemic stroke (defined by ICD-9-CM 434.0, 434.00, 434.10, 434.11, 434.9, 434.90, 434.91, 436/ ICD-10-CM I66.09, I66.19, I66.29, I66.9, I63.40, I63.50, I67.89 in the primary diagnosis position in a hospitalization or ED visit) [29]. We will utilize the same modeling strategy as used for the primary outcome.g) We will evaluate **negative control (falsification) endpoints**. Our negative control endpoint will be hospitalized/ED urinary tract infection (including renal abscess and pyelonephritis) (ICD-9-CM 590.1, 590.11 590.2, 590.8 or 599.0/ ICD-10-CM N15.1, N39.0, N10). We will utilize the same modeling strategy as used for the primary outcome [30].h) We will perform several sensitivity analyses for outcome ascertainment.

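### On the plain wording of the Aim 1 washout, new AF coded once in clinic before an AF admission is dropped as a case, and the sections disagree on the anchor

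*Protocol article*

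**What the plan says.** In the protocol article, Inclusion and exclusion criteria (Aim 1) finds cases by "ICD-9-CM code 427.31 or ICD-10-CM code I48 in 2 outpatient claims or 1 inpatient claim within 365 days". It dates them by this rule: "The index date will be the date of the first qualifying inpatient claim or second qualifying outpatient claim". The washout follows directly: "Patients will be required to have 12 months of FFS claims without an AF diagnosis prior to the index AF claims based on inclusion criteria".

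Other statements bear on where the washout starts. The same section treats diagnosis and index date as one event when it asks for "continuous enrollment in fee-for-service (FFS) Medicare after AF diagnosis/index date for at least 12 months". Analytical cohort does likewise: for cases, "the date of AF diagnosis will serve as" the index date. Regression modeling (aim 1), item a, gives a different date: "The study index date will be the date of the first AF claim in the study".

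Analytical cohort defines cases as patients who meet both the AF criteria and the other eligibility criteria. It then says: "All remaining beneficiaries will be considered potential controls". The only exclusion listed for Aim 1 is a claim for central retinal artery occlusion (CRAO) in the preceding 12 months.

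**The concern.** A washout of this kind exists to remove old AF. Counted back from the qualifying claim, it also removes some new AF. Take a patient with a first clinic claim for AF on 1 March and an AF admission on 1 June. The admission qualifies alone, so it sets the index. The March claim is an AF code inside the previous 12 months, so the patient fails.

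Two things are at stake:

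- **Selection by route of diagnosis.** AF first coded at an admission is kept, while the same new AF coded once in clinic shortly before is lost. This sits badly with the article's own rationale, which faults earlier hospital-based work for having no outpatient data and so under-ascertaining AF. Here the outpatient claim is the reason for discarding the patient.
- **Misclassification.** A patient with AF who is rejected as a case is not explicitly kept out of the comparison group.

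**Working it through.** **Inputs.** The case algorithm, index rule and washout come from Inclusion and exclusion criteria (Aim 1). The alternative index date comes from Regression modeling (aim 1), item a. The control-pool rule comes from Analytical cohort.

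**Step 1: four readings of the washout.**

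- A: counted back from the index date; any AF code counts.
- B: counted back from the earliest claim of the qualifying set (one admission, or both claims of an outpatient pair); any AF code counts.
- C: counted back from the first AF claim, following the aim 1 regression section.
- D: only AF that already meets the algorithm counts as a diagnosis.

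**Step 2: apply them to four new-AF histories.**

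| Claim history | A | B | C | D |
|---|---|---|---|---|
| Inpatient only | keep | keep | keep | keep |
| Outpatient, then outpatient at 60 days | drop | keep | keep | keep |
| Outpatient, then inpatient at 60 days | drop | drop | keep | keep |
| Outpatient, then inpatient at 400 days | keep | keep | keep | keep |

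**Step 3: which reading does the wording favour?**

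- The washout sentence speaks of claims that carry no AF diagnosis, and the case definition accepts the code in any position on a claim. That is claim-level language, which points to A or B.
- The plural in the washout sentence favours B over A, because it can cover both claims of an outpatient pair. It cannot cover a lone clinic claim, which is no part of a qualification that one admission achieves alone.
- Under D the washout has almost nothing to do. The index is the first point at which the algorithm is met, so confirmed AF can hardly precede it, except perhaps a post-operative episode set aside under Exposure.
- C requires replacing the index date of the eligibility section with that of the regression section.

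**Step 4: direction of bias if rejected AF patients become controls.** The planning rates in Sample size calculation are 22 and 11 per 100,000 per year. Let f be the fraction of control person-time that comes from patients with AF, and suppose they carry the AF rate.

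Control rate = 11(1 − f) + 22f = 11(1 + f)

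Observed ratio = 22 / [11(1 + f)] = 2 / (1 + f)

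This equals 2 at f = 0 and falls below 2 for any f above 0. The documents do not allow f to be estimated.

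**Step 5: power, as context only.** The plan states that "570,000 subjects (285,000 with AF and 285,000 without) would have 90% power to detect a hazard ratio of 2, at an alpha of 0.05". The two-sided Freedman formula, assuming one year of follow-up because no duration is given, yields:

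Events = [(1.960 + 1.282) × (2 + 1)/(2 − 1)]² = 94.6, so 95

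N = 95 / [(0.00022 + 0.00011)/2] = 95 / 0.000165 = 575,758

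That is within about 1% of 570,000, but before any allowance for the stated 20% loss; dividing by 0.8 gives 719,697. A one-sided version with 78 events gives 78 / 0.000165 = 472,727, and × 1.2 = 567,273. The present point does not depend on which was used.

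The article reports 818,940 patients with AF in a query of 2000–2015. Since 1 − 285,000/818,940 = 0.652, about 65% of that pool could go before it fell below the planned AF group. The pool is given as a count of unique AF patients, with no mention of enrolment or washout rules, so this is only a loose bound.

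**The case against.** The strongest reply is that the text need not be read at claim level. Two sections use AF diagnosis for the event that sets the index date, which suggests algorithm-confirmed AF. A single outpatient code is not AF under the algorithm, so it would not breach the washout. The regression section's first-claim index also keeps the patient. This part stands: a reader might infer that the patient fails on every reading, and the documents do not support that. It does not clear the text, because one of these readings nearly empties the washout and the other contradicts the stated index date.

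A reader might also infer that every case found through two outpatient claims is lost. That happens only under reading A, which would cancel a route the same paragraph creates. The plural wording gives a sensible alternative, so this inference should be set aside.

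It can be said that the control-pool problem is separate, since it affects anyone who fails the washout, including patients with old AF who rightly fail it. That is correct, and moving the anchor alone would not cure it. The group labels in the table shells suggest that AF-free controls are intended, but the selection rule does not say so.

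Finally, a condensed article may leave programming detail to the full plan. Here, however, the rule is stated in the article, and the trouble is how its anchor is fixed.

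**Conclusion.** The point holds on the plain wording, not on every reading. As the eligibility section is written, new AF with one clinic claim followed by an AF admission within 12 months is dropped. The regression section implies a different anchor, so the passages need to be reconciled. Taken literally, the control-pool rule also admits patients with AF who fail the washout. If AF does raise CRAO risk, that would tend to pull the hazard ratio toward 1.

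The size cannot be computed. A reader might apply a guessed share to the 818,940 patients, but the documents give no share for this pathway and do not show that the pool is incident AF. Nor do they show that power is threatened. The issue is selection and misclassification, and it merits correction because the stated rule, if followed, gives a worse cohort. The direction of bias in Step 4 assumes that misplaced AF patients carry the AF event rate; no direction is claimed for the loss of cases itself.

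**What to change.** Three linked changes:

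1. **Washout.** Require no AF claim in any setting during the 12 months before the first AF claim of the qualifying 365-day window, and count the 12 months of prior enrolment from that same date.
2. **Index date.** Keep it at the qualifying claim, and change item a of Regression modeling (aim 1) to agree.
3. **Control pool.** State in Analytical cohort that patients with AF who fail the washout cannot serve as no-AF controls.

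The cost is a few sentences and a small change in cohort code. Some patients will need slightly longer prior enrolment, because the look-back starts from an earlier date, and a few may be lost for that reason. The change is best made before the primary analysis is run.

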### Inclusion and exclusion criteria (Aim 2)

Inclusion criteria are fee-for-service Medicare enrollment for at least 12 consecutive month and 12 months FFS with Part A, B, and D enrollment following the index date for at least 12 months or until death, and presence of atrial fibrillation as defined in the exposure section. The index date for patients exposed to anticoagulation will be the date of the first anticoagulant prescription drug claim occurring after the diagnosis of AF. For potential controls, only patients with no exposure to anticoagulation throughout the study period would be eligible to avoid selecting controls who start an anticoagulant during the follow-up period. For controls, inclusion and exclusion criteria will be examined for each year after AF diagnosis, and the midpoint of one random year will be selected as the index date for each control patient.

Exclusion criteria include:

Patients with any claim for CRAO in the 12 months prior to AF diagnosis or index date for controls;Patients who die within first 12 months of enrollment;Patients taking therapeutic-dose heparin, enoxaparin, dalteparin, fondaparinux, or betrixaban.

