### Exposure

The primary exposure of interest is prevalent atrial fibrillation/atrial flutter. Atrial fibrillation/atrial flutter will be defined through ICD-9-CM 427.13 or ICD-10-CM code I48 in 2 outpatient claims or one inpatient claim within 365 days [16–18]. Episodes of atrial fibrillation within 1 month of inpatient surgery will be excluded to avoid including patients with isolated post-operative atrial fibrillation [19].

The secondary exposure of interest (among patients with atrial fibrillation) is exposure to anticoagulation. For our secondary analysis (Objective 2), we will utilize Medicare Part D prescription drug claims to identify patients taking a direct acting oral anticoagulant (DOAC) or warfarin.

A list of search terms to identify anticoagulant drugs will be utilized as per Table 1, below:

**Table 1 pone.0296251.t001:** Drug lookup queries for anticoagulant exposure.

Drug Name	
Warfarin	Part D claim for generic drug name like ‘%WARFARIN%’, summarized per month (90-day fills will be imputed to monthly indicators)
Apixaban	Part D claim for generic drug name like ‘%APIXABAN%’, summarized per month (90-day fills will be imputed to monthly indicators)
Dabigatran	Part D claim for generic drug name like ‘%DABIGATRAN%’, summarized per month (90-day fills will be imputed to monthly indicators)
Edoxaban	Part D claim for generic drug name like ‘%EDOXABAN%’, summarized per month (90-day fills will be imputed to monthly indicators)
Rivaroxaban	Part D claim for generic drug name like ‘%RIVAROXABAN%’, summarized per month (90-day fills will be imputed to monthly indicators)

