#### Regression modeling (aim 2)

a) In keeping with target trial emulation methodology as described above, the index date for patients exposed to anticoagulation will be the date of the first anticoagulant prescription drug claim occurring after the diagnosis of AF. For potential controls, only patients with no exposure to anticoagulation throughout the study period would be eligible to avoid selecting controls who start an anticoagulant during the follow-up period. For controls, inclusion and exclusion criteria will be examined for each year after AF diagnosis, and the midpoint of one random year will be selected as the index date for each control patient.b) Similar to Aim 1, patients diagnosed with CRAO precedent to or concurrent to AF diagnosis will be excluded and these patients will be examined in an exploratory analysis.c) Our primary analysis will utilize propensity score overlap weighting methodology to approximate a randomized design where baseline hazard of CRAO of patients receiving anticoagulation vs. not receiving is comparable. We will incorporate the following variables to define the propensity score: age, time since first AF claim, sex, geography, race, Medicaid dual eligibility, vascular comorbidities and non-vascular comorbidities relevant to the likelihood that a patient will be treated with anticoagulation (to include all of the comorbidity variables included for Aim 1 propensity score, as well as history of gastrointestinal bleeding or peptic ulcer disease (using validated ICD-9-CM codes 531.x (gastric ulcer), 532.x (duodenal ulcer), and 578.x (gastrointestinal hemorrhage) and their ICD-10-CM counterparts K25.x, K26.x, and K92.2) and history of intracranial hemorrhage (any of ICD-10-CM I60, I61, S06.3, S06.4, S06.5, S06.6 and their ICD-9-CM counterparts 430.x, 431.x, 432.x)) [32–35].d) Our principal effect of interest is the hazard of CRAO among patients treated with any oral anticoagulant agent compared to those not treated. Given variable patient adherence to anticoagulation, we will take advantage of the strength of Part D data (which records pharmaceutical fills rather than prescriptions) and treat anticoagulation exposure as a time-varying covariate for patients exposed to anticoagulation.e) We will perform identical sensitivity analyses as described in Aim 1.f) Table shells for the results of Aim 2 are shown in Table 8.

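### Aim 2 classifies exposure from Part D fills, but Part D is required for only 12 months after index and its loss is not among the listed censoring events

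*Protocol article*

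**What the plan says.** **Source of exposure.** Under Exposure, the protocol article states that "we will utilize Medicare Part D prescription drug claims to identify patients taking a direct acting oral anticoagulant (DOAC) or warfarin". Table 1 adds that claims for each drug are "summarized per month (90-day fills will be imputed to monthly indicators". No other source of exposure is named.

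**Use in the model.** Under Regression modeling (aim 2), item d, the plan is to "treat anticoagulation exposure as a time-varying covariate for patients exposed to anticoagulation". Table 8 reports the Aim 2 hazard ratios on that basis.

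**Part D requirement.** The Aim 2 inclusion criteria require "12 months FFS with Part A, B, and D enrollment following the index date for at least 12 months or until death". They set no Part D condition after that.

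**Controls.** Regression modeling (aim 2), item a, says that "only patients with no exposure to anticoagulation throughout the study period would be eligible".

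**End of follow-up.** Under Analytical cohort: "Patients will be censored at death, at the end of fee-for-service enrollment, or at the end of data availability". Regression modeling (aim 1), item b, repeats the same three events: "with patients censored at death, at end of data availability, or at end of fee-for-service Medicare enrollment". There is also a late cut-off: "When 85% of the cohort has died or been lost to follow-up, we will censor remaining patients at that point". The Aim 2 modeling section contains no censoring rule.

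**The concern.** A month can be classified as on or off drug only if a fill in that month would be visible. Visibility depends on Part D, whereas time at risk, under the listed events, depends on fee-for-service enrollment. The two windows are guaranteed to coincide for 12 months and may then separate.

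The outcome does not depend on Part D. CRAO is found in emergency department, inpatient and outpatient claims, so a patient without Part D can still have a counted event. A treated patient who leaves Part D but continues the drug under other coverage would add person-time and events to the unexposed side. A control who leaves Part D could start an anticoagulant unseen and remain classed as never exposed.

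At stake is the principal Aim 2 comparison. The same coding also feeds the ischemic stroke and intracranial hemorrhage results in Table 8, which the Limitations section uses to judge whether the CRAO result can be believed.

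**Working it through.** **1. The two windows side by side**

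| Item | Where stated | Depends on |
|---|---|---|
| Exposure status each month | Exposure, Table 1; Regression modeling (aim 2), d | Part D |
| Required Part D after index | Inclusion and exclusion criteria (Aim 2) | 12 months, or until death |
| Outcome | Outcome | Emergency department, inpatient and outpatient claims |
| End of follow-up | Analytical cohort; Regression modeling (aim 1), b | Death, fee-for-service, data end |
| Late cut-off | Analytical cohort | 85% of the cohort dead or lost |

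Nothing limits follow-up to 12 months, and the 85% cut-off implies that it can run well beyond. From month 13, a patient with fee-for-service but no Part D is at risk, can have an event, and has no observable fills. Nothing in the text separates that state from having stopped the drug. That such months would be coded off drug is an inference from the fill-based monthly indicator; the article does not say so.

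**2. Size and direction**

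The article gives no sample size, effect size or rate of Part D loss for Aim 2, so there is no figure of its own to reproduce. The following is an illustration on assumed inputs.

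- HR: the true hazard ratio, on drug versus off drug.
- f: the share of all person-time coded unexposed that is really treated time (assumed).
- r: the baseline CRAO hazard of Part D leavers relative to stayers (assumed).

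With the off-drug hazard of stayers set to 1, the on-drug hazard is HR. The unexposed-coded hazard is the mixture (1 − f) + f × r × HR. Hence

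observed HR = HR / [(1 − f) + f × r × HR].

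With r = 1, meaning that leaving is unrelated to CRAO risk:

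| True HR | f = 5% | f = 10% | f = 20% |
|---|---|---|---|
| 0.50 | 0.50/0.975 = 0.513 | 0.50/0.950 = 0.526 | 0.50/0.900 = 0.556 |
| 0.70 | 0.70/0.985 = 0.711 | 0.70/0.970 = 0.722 | 0.70/0.940 = 0.745 |

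**3. When the direction reverses**

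The observed value moves away from 1 when the denominator exceeds 1, that is when r × HR > 1, or r > 1/HR. The threshold is r > 2.0 for a true HR of 0.50, r > 1.43 for 0.70 and r > 1.11 for 0.90. For example, with HR = 0.50, f = 10% and r = 2.5, the denominator is 0.90 + 0.10 × 1.25 = 1.025 and the observed value is 0.488.

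**4. Effect of censoring at the end of Part D**

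This sets f from this source to 0, and the observed value in the illustration returns to the true HR.

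**The case against.** The strongest objection is that the censoring list was written around Aim 1. The Analytical cohort section builds the AF and non-AF groups and a propensity score for AF status, and the repeat stands under Aim 1 modeling. The Aim 2 section says nothing on censoring, and a condensed article may leave this to a fuller document. A 12-month minimum is also an entry condition. Aim 1 requires 12 months of fee-for-service and then censors when fee-for-service ends; by analogy, Aim 2 might censor when its own required coverage ends. Table 4 calls the cohort Part D enrolled, and the end of data availability could be stretched to cover Part D data.

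Part of this stands. A reader might infer that the plan has decided to keep patients in Aim 2 after Part D ends and to code them untreated. The article does not say that. What remains is that the only list of censoring events it gives, stated twice, does not fit the Aim 2 exposure, and no other is offered. Reading data availability as Part D enrollment is strained when another enrollment event is listed separately beside it.

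Two further objections are sound. Patients who leave fee-for-service are already censored under the list, so only those who keep it, lose Part D and take the drug contribute. And f is a share of all unexposed-coded time, including never-treated controls and true off-drug months, which keeps it down.

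**Conclusion.** The mismatch is real and should be corrected. Exposure can be observed only under Part D, Part D is assured for only 12 months after index, and no listed event ends follow-up when it is lost.

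The size is unknown. If 5 to 20% of unexposed-coded time were really treated and leavers had the same baseline risk as stayers, a true 0.50 would be estimated at 0.51 to 0.56 and a true 0.70 at 0.71 to 0.75. These shifts are modest and would not by themselves hide a protective effect of that size.

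A reader might infer a certain bias toward no effect. The documents do not support that. The direction rests on leaving Part D being unrelated to CRAO risk, and it reverses if leavers' baseline hazard exceeds 1/HR times that of stayers. For a weak true effect, such as 0.90, a baseline hazard just over 1.11 times as high is enough. The stroke and hemorrhage results share the same exposure coding, but the effect on them cannot be quantified from the article.

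**What to change.** State a censoring rule for Aim 2 that adds the end of Part D enrollment to the existing events, for treated patients and controls alike. Exposure is then classified only in months when a fill could be seen. Apply the controls' no-exposure check only to months with Part D coverage. No separate Part A or B clause is needed if the fee-for-service event applies to Aim 2, since it largely covers this; say that it does apply.

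The cost is a sentence or two and a monthly enrollment check, using the same kind of enrollment information that the inclusion criterion already needs. Some late follow-up and some events are lost. Censoring at loss of Part D also assumes that, given the covariates, leaving is not informative about CRAO risk. Reporting how many patients in each group are censored for this reason would let readers judge that, and would supply the share that the article does not give.

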### Design and setting

Retrospective, observational, population-level cohort study of patients with atrial fibrillation and matched controls using administrative claims data among a 5% sample of fee-for-service Medicare beneficiaries in the United States from 2000–2020. This data source allows us to follow unique patients longitudinally for the duration of their fee-for-service enrollment, regardless of state of residence.

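### Aim 2 requires Part D coverage only after the index date and has no anticoagulant-free look-back, so continuation fills can become time zero and control non-exposure is checkable only in covered months

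*Protocol article*

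**What the plan says.** The Aim 2 eligibility section has two enrollment clauses. The first asks for "fee-for-service Medicare enrollment for at least 12 consecutive month"; it names neither Part D nor the index date. The second asks for "12 months FFS with Part A, B, and D enrollment following the index date for at least 12 months or until death"; it names Part D but places it after index.

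Time zero for the anticoagulated group is "the date of the first anticoagulant prescription drug claim occurring after the diagnosis of AF". For the comparison group, "only patients with no exposure to anticoagulation throughout the study period would be eligible", and "the midpoint of one random year will be selected as the index date for each control patient".

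Drug exposure comes from one source. Under Exposure, "we will utilize Medicare Part D prescription drug claims to identify patients taking a direct acting oral anticoagulant (DOAC) or warfarin". The study covers "fee-for-service Medicare beneficiaries in the United States from 2000–2020". Item a of Regression modeling (aim 2) repeats the index-date rules and introduces them with "In keeping with target trial emulation methodology as described above".

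**The concern.** A target trial emulation has eligibility, treatment assignment and the start of follow-up coincide. If the first post-AF claim is time zero but may be a refill of treatment begun earlier, the exposed group mixes people starting treatment with people who have already tolerated it, stayed on it and had no recent CRAO claim. The effect estimated for that mixture is not the effect of starting treatment, and the mix is unknown.

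In the comparison group, a month without Part D coverage yields no anticoagulant claims whether or not the patient takes the drug. A control could then be classed as never exposed because nothing was recorded. Aim 2 carries the protocol's whole answer on whether anticoagulation modifies CRAO risk, and the Limitations section relies on the careful choice of index date and controls to support it.

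**Working it through.** **Step 1: is pre-index drug history required anywhere?**

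| Place in the protocol | What it fixes | Does it close the gap? |
|---|---|---|
| Aim 2 eligibility, first clause | 12 consecutive months of fee-for-service, no anchor | No. Even if read as pre-index, Part D is not named |
| Aim 2 eligibility, second clause | Parts A, B and D after index | No. Post-index only |
| Aim 2 exclusions | Heparin, enoxaparin, dalteparin, fondaparinux, betrixaban | No. Warfarin and the four DOACs of Table 1 are not listed |
| Aim 1 eligibility | 12 months free of AF diagnoses | No. It concerns diagnoses, not drugs. Aim 2 takes its AF definition from Exposure, which does not repeat it |
| Regression modeling (aim 2), item c | Time since first AF claim in the propensity score | No. It does not measure prior anticoagulant use |
| Regression modeling (aim 2), item d | Time-varying exposure in the exposed group | No. It acts only during follow-up |

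**Step 2: who can enter on a continuation fill?** (i) A patient anticoagulated for another reason before AF. (ii) A patient with AF and anticoagulation before Part D coverage. (iii) If Aim 2 uses the Aim 1 dating rule, under which outpatient AF is dated at the second qualifying claim within 365 days, a patient who started treatment between the two claims. The stated rules admit all three.

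**Step 3: what can be checked in controls?** The criterion spans 2000–2020. Guaranteed Part D coverage spans 12 months after a randomly chosen index date, or until death. Any visible fill disqualifies a control; a fill in an uncovered month cannot be seen.

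**Step 4: size.** The plan gives no power calculation or expected hazard ratio for Aim 2, so there is no figure to reproduce. The following values are assumptions.

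*Continuing users.* Let a share q of the exposed group be continuing users whose CRAO hazard is r times that of true starters. The hazard ratio is multiplied by 1 − q(1 − r):

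- q = 0.3, r = 0.7: 1 − 0.3 × 0.3 = 0.91
- q = 0.5, r = 0.6: 1 − 0.5 × 0.4 = 0.80
- q = 0.3, r = 1.3: 1 + 0.3 × 0.3 = 1.09

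*Unseen exposure in controls.* Let a share m of controls be anticoagulated but unseen. The observed hazard ratio is HR / [(1 − m) + m × HR]:

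| Assumed true HR | m = 5% | m = 10% | m = 20% | m = 40% |
|---|---|---|---|---|
| 0.50 | 0.513 | 0.526 | 0.556 | 0.625 |
| 0.70 | 0.711 | 0.722 | 0.745 | 0.795 |

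*Both together.* With true HR 0.50 and m = 20%, the control factor is 0.556 / 0.50 = 1.11. Multiplied by 0.91 it gives 1.01, almost no net shift; multiplied by 1.09 it gives 1.21, a clear shift toward 1.

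**The case against.** The strongest reply is that the enrollment sentence is garbled. It states a duration twice and leaves the first 12 months without an anchor, so words may be missing. By analogy with Aim 1, the first clause probably means the period before index. Table 4 describes a Part D-enrolled cohort at first eligibility and has rows for antiplatelet, lipid-lowering, hypoglycemic and antihypertensive drugs, which suggests that pre-index Part D data may have been intended. This stands in part: pre-index Part D is somewhat ambiguous. Table 4 is also not proof of a contradiction, because it includes an oral anticoagulant row and so is not clearly confined to pre-index use. The ambiguity does not supply the missing exclusion of earlier oral anticoagulant fills, which appears nowhere.

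A second reply is that the protocol never speaks of new users, and its contrast is treated versus untreated with time-varying fills. That is true of the wording. But time zero at the earliest post-AF fill, within a claimed target trial emulation, gives that fill the role of treatment start.

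Two stronger readings should be resisted. A reader might infer that continuing users bias the result toward apparent protection. That requires r below 1, which the documents do not establish: no early CRAO risk period after starting treatment is described, patients anticoagulated for other reasons may be at higher embolic risk, and controls too have survived some time after AF diagnosis. A reader might also infer that control non-exposure cannot be verified at all. Non-exposure through Part D is observable in the required 12 months after index, or until death.

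**Conclusion.** The point holds as a design weakness in the stated eligibility rules. As written, Part D is required only after index, earlier warfarin or DOAC fills do not exclude, and continuation fills can set time zero. Control non-exposure over the study period is verifiable only in covered months. Neither the propensity score nor the time-varying exposure repairs this.

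Size and net direction are unknown. On the assumed values above, continuing users multiply the hazard ratio by 0.80 to 1.09, and unseen exposure in controls moves a true 0.50 to between 0.513 and 0.625. The two can offset or reinforce each other. The documents give none of q, r, m or an expected hazard ratio, so these figures show only that the effect could matter. The change should be made, because the bias could not be corrected afterwards from the data that eligibility guarantees.

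**What to change.** In the Aim 2 eligibility section:

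1. Require 12 months of continuous Part A, B and D before index in both groups, and rewrite the enrollment sentence so that the pre-index and post-index periods are separate and each names its parts. This also supports the baseline drug rows in Table 4.
2. Exclude patients with any oral anticoagulant fill in that window before the index fill.
3. Define control non-exposure over Part D-covered months rather than over the whole study period.
4. State which AF date anchors the search for the index fill in Aim 2.

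The cost is a change to eligibility programming and the loss of prevalent users and of patients, with their events, who have under 12 months of pre-index Part D. That loss matters, since the Limitations section stresses how rare CRAO is. Keeping the cohort without the look-back as a sensitivity analysis would show how much the restriction changes the estimate. The timeline places the primary analyses after publication of the protocol, so under that plan the rule could be fixed before results were seen.
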